### Preoperative workup

Before surgery (1 to 3 months prior to surgery), the patients will have a thoracic and abdominal computed tomography (CT) scan and pelvic MRI for routine oncologic evaluation. CT scan will be performed with endovenous and rectal iodinated contrast. In addition, a digital examination and rectoscopy will be performed. Rectoscopy will assess the grade of colitis (Harig scoring system) [25]. During rectoscopy, if there are changes in the mucosa or anastomosis, such as inflammatory areas or suspicious malignancy, biopsies will be performed according to the usual care of all patients with rectal cancer during oncological follow-up. These procedures are already performed for the usual routine service management before ileostomy closure.

All patients will then undergo a standardized preoperative clinical and anesthesiological evaluation.

### Surgical techniques and surgeons

Five experienced surgeons will perform the procedures (all performed more than 50 ileostomy closures).

Patients will have 8 h of fasting. Infusion of second-generation cephalosporins will be performed intravenously during anesthetic induction before the procedures.

The initial approach (total mesorectal excision with protective ileostomy) will be performed with minimally invasive access (robotic-assisted or laparoscopic) following the following technique:

1—Patient in lithotomy position under spinal anesthesia and sedation; 2—Antisepsis with alcoholic chlorhexidine solution; 3—Asepsis and placement of sterile surgical drapes; 4—Inspection of the cavity for the presence of metastases; 5—Identification, isolation, and sealing of the inferior mesenteric vein at its origin; 6—Left mesocolon detachment from retroperitoneum structures; 7—Access to the retrocavity of the epiplons, and opening of the intercolonepiploic space, with release of the splenic angle; 8—Identification, isolation, and clipping of the inferior mesenteric artery at its origin; 9—Release of left parietocolic gutter; 10—Mesorectal dissection up to the level of the levator ani muscles and posterior section of the rectum; 11—Colorectal anastomosis with Circular Stapler (CDH 29); 12—Construction of a protective ileostomy 30 cm from the ileocecal valve, in loop, with its fixation through a hole created in the right hemiabdomen, through the rectus abdominis muscle, and fixation with Vycryl 3-0; 13—Review of hemostasis; synthesis of aponeurosis and skin; 14—Dressings.

The second surgery (ileostomy reversal) will be performed at least two months after the first surgery, after adjuvant therapy (when indicated), and the following technique will be followed:

1—Patient in lithotomy position under spinal anesthesia and sedation; 2—Antisepsis with alcoholic chlorhexidine solution; 3—Asepsis and placement of sterile surgical drapes; 3—Circular incision around the ileostomy, opening in layers until the release of the ileostomy from the aponeurosis; 4—Barcelona technique anastomosis; 5—Review of hemostasis; synthesis of aponeurosis and skin; 6—Dressings.

A rectoscopy will be performed intraoperatively to assess colitis grade (Harig scoring system) [25].

### Postoperative follow-up

In both surgeries, the patient will be discharged following the Enhanced Recovery After Surgery (ERAS®) protocol [26] when there is no evidence of complications, full diet acceptance, and bowel movement or flatus. The patient will be offered a liquid diet in the immediate postoperative period (4–6 h after the surgery) and a clear liquid diet after 24 h of the surgery if the patients present no nausea or abdominal distension. The diet will consist of foods that are low in fiber and fat. Postoperatively, patients will be instructed to record symptoms of colic/abdominal pain, nausea/vomiting, diarrhea, and the general appearance of stools and gas.

The patients will be followed at least 6 months after the surgery. Patients will return after 7–14 days after surgery, followed by 1, 3 months, and 6 months. At each return visit, patients will be actively investigated and questioned regarding food acceptance, stool consistency, signs of fecal incontinence, abdominal cramping/pain, bowel movements per day, and quality of life. The relevant questionnaires will be applied at each follow-up visit.

Patients will undergo the usual tests for colorectal cancer restaging, including serum laboratory tests, CT scans, MRI, and rectoscopy.

### Outcomes

The primary outcome will be as follows: (1) incidence of adynamic ileus (the number of patients needing postoperative nasogastric tube insertion; nausea/vomiting; or intolerance to oral feedings in the first 72 h of the surgery).

Secondary outcomes will be as follows: (1) the time to intestinal transit (time to first evacuation/flatus); (2) time to start feeding; (3) length of hospital stay; (4) grade of colitis (Harig scoring system) [25]; (5) operative complications (during hospitalization); (6) direct costs; (7) stool consistency (Bristol stool scale) [27]; (8) fecal incontinence (Wexner score) [28]; (9) abdominal cramps/pain; (10) number of evacuations per day; and (11) quality of life (SF-36) [29] and low anterior resection syndrome score (LARS) [30]. The secondary outcomes 7 to 11 will be evaluated at every clinical visit during postoperative follow-up. Patients will return after 7–14 days after surgery, followed by 1, 3 months, and 6 months. Patients will be actively investigated for secondary outcomes at each return visit. The relevant questionnaires will be applied at each follow-up visit.

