## Background

A protective ileostomy is a temporary measure usually applied to reduce the severity of complications related to colorectal anastomosis in patients with rectal cancer undergoing neoadjuvant chemoradiotherapy [1]. However, ileostomy closure is associated with a high morbidity rate, and adynamic ileus is the most common complication, with an incidence of up to 32% [2–12]. This complication is associated with delayed initiation of oral diet intake, abdominal distention, more significant patient discomfort, and prolonged hospital stay [13]. The probable cause is colonic dysfunction, leading to mucosal atrophy, with the consequent loss of intestinal absorptive capacity and atrophy of intestinal muscles, inducing changes in intestinal peristalsis [14].

Abrisqueta et al. [12], in a clinical trial of 70 patients, showed that patients that stimulated the efferent ileostomy loop with 500 ml of saline plus a thicker agent (Nestlé Resource, Vevey, Switzerland) 2 weeks before ileostomy closure had a shorter time for diet acceptance (1.06 *vs.* 2.57 days), shorter mean time to defecation (1.14 *vs.* 2.85 days), lower rate of adynamic ileus (3% *vs.* 20%), and shorter hospital stay (2.5 *vs.* 4.6 days). However, the study encompassed a limited sample size, including both primary open and laparoscopic surgery. Open primary surgery can falsify the diagnosis of adynamic ileus since intestinal adhesions can contribute to postoperative food intolerance [15].

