### Sample size

Assuming that the intervention will reduce the adynamic ileus incidence after ileostomy reversal from 20 to 2.8% [12], the estimated sample is 52 patients in each study arm, considering alpha (two-sided) 0.05 and beta 0.2 [24]. Considering that our primary outcome will be a short-term endpoint, evaluated during hospitalization after surgery, we do not expect a significant loss of follow-up for the primary outcome.

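### Operative complications are counted only until discharge, which the intervention is expected to bring forward; both arms need one fixed window from ileostomy closure

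*Protocol article*

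**What the plan says.** **Complications.** The Outcomes section of the protocol article lists "5) operative complications (during hospitalization"). The return visits are at 7–14 days and at 1, 3 and 6 months. The same section states: "The secondary outcomes 7 to 11 will be evaluated at every clinical visit during postoperative follow-up". Complications are number 5, so this sentence does not cover them. A later sentence is unrestricted: "Patients will be actively investigated for secondary outcomes at each return visit".

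**Discharge and stay.** Under Postoperative follow-up, patients go home once they have no evidence of complications, accept a full diet and have passed stool or flatus. Cost assessment hypothesises savings from a shorter stay. For the trial that supplied the ileus rates, Background reports "and shorter hospital stay (2.5 *vs.* 4.6 days"). It also describes a randomized trial of probiotics through the efferent loop with similar stays in both groups, and an observational study of reinfusion with 4.9 against 5.52 (unit not printed, presumably days). Study design states that the trial is open-label.

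**Ileus.** The Outcomes definition ends "or intolerance to oral feedings in the first 72 h of the surgery", and the Abstract gives the same window. Sample size says that "our primary outcome will be a short-term endpoint, evaluated during hospitalization after surgery".

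**Feeding.** Postoperative follow-up states: "The patient will be offered a liquid diet in the immediate postoperative period (4–6 h after the surgery"). The next dietary step, after 24 h, depends on the absence of nausea and distension. The outcome is named time to start feeding, whereas Background reports time to diet acceptance for the planning trial, 1.06 against 2.57 days.

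**The concern.** A count of complications is comparable between arms only if both arms are observed for the same period. Here the period ends at discharge, and earlier discharge is one of the effects that the trial hopes to show. If it appears, the intervention arm is watched for less time and some of its later complications go unrecorded. The complication rate could then look lower with no true difference. The article describes no masking of the staff who apply the discharge criteria, so a shorter window could also arise without faster recovery. Readmission, which matters when judging whether earlier discharge is safe, falls outside the count by construction.

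Two related wordings deserve attention. The primary outcome has a fixed 72 h window, but one sentence places its assessment in hospital, and some patients may leave before 72 h. The feeding outcome may partly reflect a schedule common to both arms.

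**Working it through.** **The plan's own figure.** The sample size is not in dispute. For 20% against 2.8%, two-sided alpha 0.05 and power 0.80, the pooled-variance formula gives

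n = [1.960·√(2·0.114·0.886) + 0.8416·√(0.2·0.8 + 0.028·0.972)]² / 0.172² = (0.881 + 0.364)² / 0.02958 ≈ 52.4 per arm.

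The stated 52 is reproduced, and nothing below changes it.

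**Complications: illustration.** The inputs from Background are mean stays of 2.5 and 4.6 days, 4.9 and 5.52, and similar stays. The assumptions, none of them in the document, are the same true 30-day risk R in both arms, a constant hazard, and every stay equal to the cited mean.

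Hazard: h = −ln(1 − R)/30. Recorded in hospital: 1 − exp(−h·stay).

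For R = 20%, h = 0.2231/30 = 0.00744 per day:

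| Stay, intervention vs control | Recorded, intervention | Recorded, control | Ratio |
|---|---|---|---|
| 2.5 vs 4.6 | 1.8% | 3.4% | 0.55 |
| 4.9 vs 5.52 | 3.6% | 4.0% | 0.89 |
| equal | same | same | 1.00 |

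The ratio hardly depends on R. With 2.5 against 4.6 days, R = 10% gives 0.9% vs 1.6%, and R = 30% gives 2.9% vs 5.3%, again about 0.55. A fixed window gives 1.00 in every row.

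In patients, R = 20% means 52 × 0.20 = 10.4 events per arm over 30 days. The in-hospital count would catch 52 × 0.0184 ≈ 1.0 and 52 × 0.0336 ≈ 1.7. Under these assumptions the larger loss is of events in both arms; the distortion between arms comes on top. Surgical complications that cluster early would raise the share caught and move the ratio towards 1.

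**Ileus.** The planning trial's mean stays are 2.5 × 24 = 60 h and 4.6 × 24 = 110 h, on either side of 72 h. No SD is given. With normal stays and assumed SDs of 0.5, 1.0 and 1.5 days, 84%, 69% and 63% of intervention patients would leave before 72 h, against 0.1%, 5% and 14% of controls. If true ileus were 20% in both arms and 10%, 20% or 30% (assumed) of intervention-arm events were missed, the recorded rate would be 18%, 16% or 14%. The chance of a significant Fisher test at 52 per arm would then be 3.4%, 5.0% or 8.2%, both directions together. The false-positive rate passes the nominal 5% appreciably only when a large share of events is missed.

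**Feeding.** The first offer comes at 4–6 h in both arms. If start means first offer or first intake, little room is left for a difference. If it means progression after 24 h, recovery does enter. Diet acceptance varies with recovery by definition and is already judged at discharge.

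**The case against.** The best case against the complications point is that the ratio of stays, 4.6/2.5 = 1.84, is not a bias estimate. A patient with a complication is kept in hospital, so complications lengthen the stay, and mean stay is partly a result of the event. The illustration above ignores this. Background also cites two studies in which the stay difference is small or absent, so the largest ratio rests on one trial. Both objections stand: they limit what can be said about size. They do not change the fact that counting stops at a treatment-dependent time. The unrestricted sentence about secondary outcomes at return visits does not rescue the count, because it conflicts with the stated in-hospital limit.

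A reader might also infer that the primary outcome is counted only until discharge and so favours the intervention. The documents do not support that. The Outcomes section and the Abstract fix ileus at 72 h from surgery. The phrase about hospitalization stands in a sentence explaining why little loss to follow-up is expected. Patients leave only when they accept a full diet and have no evidence of complications, so a large share of ileus events between discharge and 72 h is unlikely, and no document figure supports one. It is also strained to assume no effect on ileus while keeping the stay gap of a trial that reported 3% against 20%.

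Nor can one say that the feeding outcome will be equal whatever the true effect. An offer is not intake, the later step depends on symptoms, and the full protocol may define start.

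**Conclusion.** The point holds for operative complications, a secondary outcome. Their window ends at a recovery-based discharge in an open-label trial that expects the intervention to shorten the stay. If it does, the bias favours the intervention. Its size cannot be fixed from the document: the illustrative ratio with no true effect runs from about 0.55 to 1.00 depending on which cited stays apply, under constant hazard, equal risk and stays at the mean. The loss of post-discharge events and readmissions in both arms follows from the wording and needs no assumption about stay differences, though how many are lost is also unknown.

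For ileus there is a wording mismatch to align, with probably small bias. For feeding, the outcome as named may discriminate poorly between arms. Neither amounts to a demonstrated bias in the primary result.

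**What to change.** 1. **Complications.** Replace the in-hospital limit with one fixed period from ileostomy closure in both arms, for example 30 days, and include readmission. Ascertain events at the 7–14 day and 1-month visits, and make the two sentences on which outcomes are assessed at visits agree. The cost is a few questions at scheduled visits; some post-discharge events will be patient-reported.
2. **Ileus.** Align the Sample size sentence with the 72 h definition, and state how the remaining hours are ascertained for patients who leave earlier, for example from the postoperative symptom record. That record covers nausea and vomiting but does not list oral intolerance, so an item would be needed. Self-report in an open-label trial without placebo should be acknowledged as a limitation.
3. **Feeding.** Measure time to acceptance of a stated diet. This changes what is recorded, not the feeding schedule or the discharge criteria.

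The sample size of 52 per arm is unaffected.

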**Fig. 1 Fig1:**
[figure not shown]
SPIRIT. Schedule of enrolment, interventions, and assessments

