### Study groups

Intervention group (with rectal stimulation): The patient will receive guided instruction in an outpatient setting. The patient will receive the necessary materials, which include 14-French rectal tubes, saline, and a source of soluble prebiotic fibers (fructooligosaccharide) with probiotics (*Lactobacillus acidophilus*, *Lactobacillus rhamnosus*, *Lactobacillus para casei*, *Bifidobacterium lactis*) (Simbioflora®; Brand: Invictus; Manufacturer: Farmoquimica; MS1666370001001 Registry). The patient will apply 500 ml of saline solution with 6 g of Simbioflora® rectally, once daily, for 15 days before the ileostomy reversal surgery. The saline solution vials will have a predetermined volume (500 ml) to guarantee that the patients use the correct volume. The patient will have weekly visits, and the researchers will provide a contact for service at any time to optimize patients’ adherence.

Control group (without rectal stimulus): The patient will be submitted to the ileostomy reversal with no previous rectal stimulus. No placebo will be applied.

In both groups, patients will be instructed to record colic/abdominal pain symptoms, nausea/vomiting, diarrhea, and gas during the 15 days prior to ileostomy closure.

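### SF-36 is scheduled only after surgery and the analysis excludes baseline adjustment, so the quality-of-life comparison gives up precision that one pre-allocation questionnaire would recover

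*Protocol article*

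**What the plan says.** Secondary outcome 11 in the Outcomes section is "quality of life (SF-36) [29] and low anterior resection syndrome score (LARS) [30". The same section fixes its timing: "The secondary outcomes 7 to 11 will be evaluated at every clinical visit during postoperative follow-up". The visits are given as "Patients will return after 7–14 days after surgery, followed by 1, 3 months, and 6 months". Postoperative follow-up agrees: "The relevant questionnaires will be applied at each follow-up visit".

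Before closure, the text describes other measurements:

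- Preoperative workup begins "Before surgery (1 to 3 months prior to surgery), the patients will have a thoracic and abdominal computed tomography" and goes on to pelvic MRI, digital examination and rectoscopy. The only score it names is for colitis: "Rectoscopy will assess the grade of colitis (Harig scoring system".
- Study groups adds a symptom diary in both arms: "patients will be instructed to record colic/abdominal pain symptoms, nausea/vomiting, diarrhea, and gas during the 15 days prior to ileostomy closure". This is kept after assignment and is not SF-36.
- Risks and inconveniences, which lists what the trial adds to usual care, names no preoperative questionnaire.

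The Statistical analysis section treats questionnaire scores as discrete variables, compares the arms by the Mann-Whitney test, and excludes adjustment for baseline characteristics.

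Fig. 1 is captioned "SPIRIT. Schedule of enrolment, interventions, and assessments". Its content was not available for this review.

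**The concern.** General quality of life differs between patients before they enter any trial. When it is measured only afterwards, all of that spread goes into the error of the comparison between arms. A score taken before allocation and used as a covariate removes the part of the spread that persists from baseline to follow-up.

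SF-36 can be completed by a patient who still has a stoma. The Wexner, LARS and stool items describe bowel function that is diverted at that time, so their postoperative-only schedule is reasonable. The protocol already grades colitis both at the workup and during the reversal operation, so it measures before and after where it wants to see change.

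The Objectives include better clinical and functional outcomes after surgery, and the Discussion gives quality of life as part of the rationale. Without a baseline, the trial cannot report how SF-36 changed from before closure in either arm. It also compares the arms with less precision than 52 patients per arm could give.

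**Working it through.** **Inputs from the protocol article.** 52 patients per arm, two-sided alpha 0.05, beta 0.2, and ileus rates of 20% and 2.8% (Sample size); 1:1 allocation (Objectives); 15 days of rectal stimulation (Study groups); first visit at day 7 to 14 (Outcomes).

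**Assumptions.** The baseline to follow-up correlation r of SF-36 is not given, so 0.3 to 0.7 is shown. The SF-36 recall period is not given, so 1 week and 4 weeks are shown.

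**1. The plan's own figure.** With pooled variance and no continuity correction, the mean rate is (0.20 + 0.028)/2 = 0.114 and

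n = [1.960 × √(2 × 0.114 × 0.886) + 0.842 × √(0.20 × 0.80 + 0.028 × 0.972)]² / 0.172² ≈ 52.4.

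This rounds up to 53 per arm, against 52 stated; power at 52 is 79.7%. The figure reproduces within one patient. It is set by adynamic ileus and does not depend on SF-36.

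**2. SF-36 precision as planned.** In SD units and by normal approximation for a difference in means, the detectable difference at 80% power is

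(1.960 + 0.842) × √(2/52) = 0.549 SD.

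Power for a difference of 0.5 SD is 72.2%. The planned rank test would differ somewhat, but the comparison below does not turn on that.

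**3. With a baseline covariate.** Adjustment multiplies the variance by 1 − r² and the detectable difference by √(1 − r²). The equivalent unadjusted size is 52/(1 − r²) per arm.

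| r (assumed) | 1 − r² | Variance cut | Detectable difference | Power for 0.5 SD | Equivalent per arm |
|---|---|---|---|---|---|
| none | 1.00 | 0% | 0.549 SD | 72.2% | 52 |
| 0.3 | 0.91 | 9% | 0.524 SD | 76.2% | 57 |
| 0.5 | 0.75 | 25% | 0.476 SD | 83.7% | 69 |
| 0.7 | 0.51 | 49% | 0.392 SD | 94.6% | 102 |

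Under the unadjusted test now planned, collecting a baseline score gains nothing by itself. Both the score and an analysis that uses it are needed.

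**4. What the first score covers.** The share of the recall window before closure is max(0, (recall − visit day)/recall).

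| Recall (assumed) | Day 7 | Day 14 | About day 30 |
|---|---|---|---|
| 4 weeks | (28 − 7)/28 = 75% | (28 − 14)/28 = 50% | 0% |
| 1 week | 0% | 0% | 0% |

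Under 4-week recall, the window reaches back 21 days before closure at a day 7 visit and 14 days at a day 14 visit. In the intervention arm it therefore covers 14 or all 15 of the stimulation days. Only the first of the four visits is affected.

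**The case against.** **The schedule figure was not available.** Fig. 1 is where a baseline questionnaire would appear, and the text says SF-36 is taken at every postoperative visit, not that it is taken nowhere else. This stands as a caveat: a reader should not conclude that no baseline will be collected. It does not remove the point, because the Statistical analysis section would leave such a score out of the comparison.

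**Randomisation already protects the comparison.** Correct. With complete data, the unadjusted comparison of randomised arms is unbiased, and the point is one of efficiency and description. The gain also rests on a correlation that the documents do not supply; at 0.3 it is only 9%. Eligibility is restricted to one disease and one treatment pathway, so the documents give no ground for assuming that general health varies unusually widely at entry.

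**The first score.** A reader might infer that the day 7 to 14 SF-36 mainly describes life before closure. The documents do not support this, because they state neither the version nor the recall period. The share is 50% to 75% under an assumed 4-week form and 0% under a 1-week form.

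A reader might also infer that the enema arm would show a spurious disadvantage at that visit. That does not follow either. If the burden of the enemas lowers the score, this is a real consequence of the assigned strategy under intention to treat. It makes the score harder to read as postoperative recovery, but the difference is not false. The documents give no size or direction for it, and the Background describes enemas as tolerated in other conditions.

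**It is one of many secondary outcomes.** SF-36 is part of the last of eleven. This limits the importance of the point, but the remedy is correspondingly small.

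**Conclusion.** The point holds as a cheap improvement to a secondary outcome. As the text stands, SF-36 is described only after surgery and the analysis excludes baseline adjustment. For an assumed correlation of 0.3 to 0.7, this forgoes a variance reduction of 9% to 49%, worth about 57 to 102 patients per arm instead of 52. The trial also loses the ability to describe change from before closure.

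The first part is subject to Fig. 1; the exclusion of adjustment is not. The point does not show bias, and it does not touch the primary outcome or the sample size. The recall calculation supports a note on interpreting one visit, conditional on the form used, and gives no sufficient reason to drop that visit.

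**What to change.** 1. Add one SF-36 at the consent visit, before allocation, in both arms, and say so in the Outcomes section. If Fig. 1 already lists it, bring the text into line. The consent visit is the safer place, because the text does not say whether the workup, 1 to 3 months before surgery, falls before or after allocation.
2. Keep all four postoperative SF-36 assessments as planned, and leave LARS, Wexner and the stool items at the postoperative visits.
3. Compare postoperative SF-36 scores with adjustment for the baseline score, by ANCOVA or a rank-based equivalent, and state this as an exception to the no-adjustment rule in Statistical analysis. Raw change scores are not a substitute: with equal variances their variance factor is 2(1 − r), which exceeds 1 when r is below 0.5 (1.4 at r = 0.3).
4. State the SF-36 version and recall period. If recall is 4 weeks, note when interpreting the day 7 to 14 score that half to three quarters of its window precedes closure.

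The cost is one extra short questionnaire per patient at an existing contact and a change of analysis method for this outcome. No new visit or staff is needed. Moving the day 7 to 14 questionnaire to baseline would avoid the extra form but lose the only score from the first two postoperative weeks, so adding one is preferable.
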